As the developers of Skin NTDs App have ambitious plans and expectations, it is essential to conduct a rigorous and validated assessment of this app. This paper describes the protocol for a cross-sectional study aimed to assess the engagement, functionality, aesthetics, and quality information for the real end user in their actual context of version 3 of Skin NTDs App in accordance with a validated tool. In addition, a secondary goal of this study will be to determine whether any of the demographic information collected has an impact on the final uMARS score, since the developers of Skin NTDs App do not intend to customize the app when implementing it in any setting.

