### Outcomes

#### Demographic Variables

Participants will be asked to complete an anonymous survey of various demographic data, which will include the following: age, gender (“Male,” “Female,” “nonbinary,” and “transgender”), country of residence (“Ghana” and “Kenya”), type of FHWs (3 specified categories will be provided as these are most common: “Medical Doctor,” “Nurse,” “Community Health Worker,” and “Other” under which participants will be asked to add their own category), frequency of dealing with skin NTDs [“Rarely (<1 case/month),” “Occasionally (1-3 cases/month),” “Frequently (4-6 cases/month),” and “Usually (>6 cases/month)”], experience and training in dermatology (“Trained and experienced,” “Not trained but with experience with dermatology patients,” and “Neither trained nor experienced”), work environment (“rural” and “urban”), working institution (“Public healthcare setting,” “Private healthcare setting,” and “NGO”), knowledge of mobile technology (“High—I’m able to use mobile technologies without having many issues,” “Medium—I’m able to use mobile technologies but sometimes I need some help,” and “Low—I’m not able to use mobile technologies without supervision and help”), and languages (open answer for participants to enter the languages they can speak).

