#### uMARS Questionnaire

The uMARS is a simple, objective, and reliable tool developed for users by Stoyanov et al [12] to classify and assess the quality of health-related mobile apps. The tool assesses 20 items clustered into 4 objective subscales (engagement, functionality, aesthetics, and information quality) and 1 subjective subscale. Participants rate each item using a Likert scale from 1 to 5 (1=“Inadequate,” 2=“Poor,” 3=“Acceptable,” 4=“Good,” and 5=“Excellent”). There is also the option “not applicable” if an item cannot be assessed. There is an extra category entitled *App-Specific* with descriptive purposes only that contains 5 more items and can be adjusted and adapted by researchers. This category evaluates the perceived impact of the app on users’ knowledge, attitudes, intentions to change, and the likelihood of actual change. We will add 9 questions to complete this domain, relating to app discovery, time using the app, frequency of use, notification updates, usefulness, translation features, patient record features, and desktop version.

The uMARS score is calculated separately based on the original recommendation from the authors of this scale. Hence, 2 scores will be obtained: app quality mean score and app subjective quality score. This division is made to strengthen the objectivity of the uMARS as a measure of app quality. All those questions rated as “not applicable” will be excluded from the mean scores.

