### Statistical Analysis

Quantitative data will be collected in Excel (Microsoft Inc) to be analyzed using SPSS for Windows (version 25; SPSS Inc). Statistical significance for all tests will be set at a *P* value of ≤.05. To describe the quantitative information received from the uMARS scores, a descriptive analysis will be carried out. Measures of frequency, central tendency, and dispersion will be used to describe this data, which will be shown in tables. Depending on sample size, a Shapiro-Wilk or Kolmogorov-Smirnov test will be used to assess the normality of data (*P*≤.05). In the bivariate analysis, a chi-square test will be used to compare categorical variables. Depending on whether the distribution is normal, quantitative data will be compared using a Student *t* or Mann-Whitney *U* test. A multivariate analysis will be performed using a logistic regression analysis to add the covariates that could skew the main association under analysis. Finally, a cluster analysis will be performed to identify similar groups based on the observed values of several variables. A 95% CI will be assumed and *P*≤.05 will be considered to indicate a significant difference.

Selected quotes will be returned to participants for approval. Qualitative data derived from the semistructured interviews will be analyzed using ATLAS.ti (Scientific Software Development GmbH). We will identify attributes, cluster them into different themes, and then code these themes to analyze the various dimensions explored during the interviews.

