### Limitations

There are various limitations associated with this study.

The first limitation that arises and may seem relevant is the decision behind choosing Ghana and Kenya to perform this study. This was based on 3 factors: (1) Skin NTDs App can only be downloaded in English; hence, the choices are limited to countries where English is an official language; (2) these 2 countries have a long history of web-based disease tracking and are endemic for at least 8 skin NTDs each; and (3) to ensure an adequate sampling, countries were chosen on the basis of the accessibility to key officials and program managers and their chances to further contact enough respondents.

Regarding the methodology used, snowball sampling is a nonprobabilistic and nonrandomized method; hence, the sample may not be representative of the general population. However, because the study will be conducted entirely on the internet and the participants and authors are in different places, this is the only way we can connect with FHWs—a highly specialized group that can be challenging to reach in LMICs if contacted remotely.

On the other hand, it is also important to point out some limitations of the uMARS. First, this tool has only been validated among young people using 2 specific apps related to other health areas. However, its high reliability and the inclusion of both objective and subjective domains make it the only questionnaire available that is validated and simple for users to assess health apps.

Another requirement is that FHWs will have to use the app for at least 5 days as opposed to the 10 minutes originally required by the original uMARS publication. Since there will not be any direct control over that, this statement cannot be guaranteed. To determine whether they have fulfilled it or not, a question has been added to the survey.

Finally, it is important to highlight that this study does not claim to assess the clinical effectiveness of Skin NTDs App. This would require a randomized clinical trial and exceed the scope of this study. Although this is version 3, there are still issues to address, including whether information in the app is updated in response to the most recent research.

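### No inferential method named in the protocol relates age to the numeric uMARS score without cutting either age or the score, and no cut-point is given for either

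*Protocol article*

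**What the plan says.** All references are to the protocol article.

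- **Objective (Introduction).** The secondary goal is to "determine whether any of the demographic information collected has an impact on the final uMARS score".
- **Predictor (Demographic Variables).** The survey collects "various demographic data, which will include the following: age, gender" and further items. The closed items have their response options printed and languages is marked as a free answer. Age has neither.
- **Outcome (uMARS Questionnaire).** Items are rated 1 to 5 and "2 scores will be obtained: app quality mean score and app subjective quality score". Items marked not applicable are left out of the means. Both scores are therefore numeric.
- **Methods (Statistical Analysis).** For bivariate work, "a chi-square test will be used to compare categorical variables". For numeric data the rule is: "Depending on whether the distribution is normal, quantitative data will be compared using a Student" *t* or Mann-Whitney *U* test. Then: "A multivariate analysis will be performed using a logistic regression analysis to add the covariates that could skew the main association under analysis". A cluster analysis follows. The section names no correlation and no linear or rank-based regression.
- **Limitations.** On the questionnaire, the authors note that "this tool has only been validated among young people using 2 specific apps related to other health areas".

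**The concern.** The Statistical Analysis section does more than leave the age analysis open. It sets a rule by data type, and its rule for numeric data is a two-group comparison. That rule does not fit a numeric predictor and a numeric outcome, yet age against the score is within a stated objective.

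Two things are at stake. First, with about 50 respondents, reducing a numeric variable to two groups discards information that the study can hardly spare. Second, no cut-point is given for age or for the score, so an analyst who must cut one of them can pick the split after seeing the data, under a P≤.05 rule. A null age result has consequences here, because the Introduction ties this goal to the developers' intention not to customise the app by setting.

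**Working it through.** **1. The plan's own figure.** Sample Size Calculation: 100 × (1 − 0.50) = 50, which reproduces. The Abstract gives 48; this changes little below except for the chi-square row. The protocol states no effect size or power.

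**2. Each named method against the task (numeric age, numeric score).**

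| Method | What it needs | What must be cut |
|---|---|---|
| Chi-square | two categorical variables | age and score |
| Student t / Mann-Whitney | one numeric variable, two groups | age or score |
| Logistic regression | categorical outcome | score (age may stay in years) |
| Cluster analysis | several variables | nothing, but it groups people and does not test an age-score association |

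So none of these tests the association with both variables intact. The Results section's expectation of a score above 3 is a forecast, not an analysis threshold.

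**3. Cost of cutting.** Assumptions, since the documents give none: age and score bivariate normal; true correlation r = 0.3, 0.4 or 0.5; two-sided alpha 0.05; splits at the median. Simulated power at n = 50 (20,000 runs; 1,500 for logistic regression):

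| Analysis | r = 0.3 | r = 0.4 | r = 0.5 |
|---|---|---|---|
| Both numeric (Pearson) | 0.58 | 0.84 | 0.97 |
| Age split, t test | 0.39 | 0.63 | 0.84 |
| Score split, logistic, age in years | 0.41 | 0.66 | 0.85 |
| Both split, chi-square | 0.37 | 0.56 | 0.75 |

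Before rounding, cutting one variable costs between 0.968 − 0.853 = 0.115 (r = 0.5, score cut) and 0.838 − 0.633 = 0.205 (r = 0.4, age cut), so roughly 11 to 21 points.

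If Spearman correlation is used instead of Pearson, a further simulation (10,000 runs, same assumptions) gives about 0.52 / 0.78 / 0.94. This is a little lower than Pearson but still well above every split analysis.

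**4. Check by formula.** A median split of a normal variable multiplies the correlation by √(2/π) = 0.798, which keeps 2/π = 0.637 of the information, as if n fell from 50 to 50 × 0.637 ≈ 32. Fisher-z power is Φ(atanh(r)·√(n − 3) − 1.96). At r = 0.40 and n = 50:

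- uncut: 0.4236 × √47 = 2.904; 2.904 − 1.960 = 0.944; power 0.828
- age split: r becomes 0.40 × 0.798 = 0.319; atanh = 0.3307; × √47 = 2.267; 2.267 − 1.960 = 0.307; power 0.621

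Both agree with the simulation (0.84 and 0.63).

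**5. Caution on the chi-square row.** With both variables split 25/25, the statistic is 0.08(2a − 25)², where a is the count in one concordant cell. It first passes 3.84 at a = 16 (3.92). Under no association, the hypergeometric chance of a ≥ 16 or a ≤ 9 is 0.089, so the nominal 5% test runs near 9% and its power is flattered. At n = 48 the true level is 0.042 and power is 0.24 / 0.42 / 0.61.

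**The case against.** **Logistic regression accepts age in years.** This is correct, and a t or Mann-Whitney test could likewise compare uncut age between two score groups. A reader might infer that age itself must be dichotomised or dropped; the documents do not support that. In each of these routes, however, the score has to be cut instead, at a point nobody has fixed, and the power loss is of similar size.

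**The age format is not stated.** This stands. That age is numeric is inferred from the missing answer options, and the survey form is not shown. If age is collected in bands, the first step is to collect it in years.

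**A condensed article may leave the procedure for one covariate to a fuller plan.** This stands in part and keeps the point modest. But the section does name tests by data type, and its rule for numeric data does not fit this objective. That goes beyond silence.

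**Age is not singled out by the authors.** This stands. The Results section suspects dermatology experience and mobile technology use, not age. A reader might also infer from the Limitations section that an age trend is the main check on whether ratings can be pooled. The text does not support this: its doubt equally concerns the apps and health areas used in validation. Older workers may also genuinely rate the app differently, and the absence of a trend would not show that the tool is valid in them.

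**Conclusion.** The point holds in this form: age falls within a stated objective, and no inferential method in the Statistical Analysis section relates it to the numeric score with both kept numeric. At n = 50 the power loss from cutting one variable is roughly 11 to 21 percentage points over assumed correlations of 0.3 to 0.5. These figures rest on normality, median splits and correlations chosen here for illustration; an uneven split would lose more (an 80/20 cut keeps about 49% of the information). The freedom to choose the cut after seeing the data does not depend on those assumptions.

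The result is relevant, though not decisive, to the authors' own note that the questionnaire was validated only in young people. This is a worthwhile and nearly free improvement, not a flaw that threatens the main descriptive aim.

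**What to change.** In Statistical Analysis, state that age will be recorded in years and related to each of the two uMARS scores, both kept numeric, by Spearman correlation or by a linear regression slope (for example per 10 years), with a 95% CI and a scatter plot. Add that any adjusted model of the score keeps age and score uncut, which means a linear or rank-based model for that purpose in place of logistic regression on a dichotomised score.

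The cost is a sentence or two in the analysis section and one extra routine analysis. No new data are needed if age is already collected in years.

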## Results

The results of this work are expected during the third quarter of 2022. First, Skin NTDs App version 3 is expected to obtain a result of >3 out of 5 points on the uMARS. In addition, it is expected that the results will not show any difference by sex, type of work environment or working institution, or country. However, it is suspected that those variables related to experience in dermatology or the use of mobile technology may be determining factors when evaluating the user experience with the App. On the other hand, the perceptions collected from the semistructured interviews are expected to be the element to understand the reason for the results obtained on the uMARS.

Moreover, they will be the previous step before assessing other aspects of the App, such as the efficiency, how it should be disseminated or implemented, etc.

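### Logistic regression is the only adjusted analysis, but the secondary aim's outcome is a mean uMARS score with no binary or ordinal form defined and no main association designated

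*Protocol article*

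**What the plan says.** The Introduction sets the secondary goal: to "determine whether any of the demographic information collected has an impact on the final uMARS score". The uMARS Questionnaire section gives the scale: "Participants rate each item using a Likert scale from 1 to 5". It then gives the form of the outcome: "2 scores will be obtained: app quality mean score and app subjective quality score". Items marked not applicable are left out of the means.

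The Statistical Analysis section handles scores of this kind as quantitative in the bivariate step, where "quantitative data will be compared using a Student *t* or Mann-Whitney *U* test", depending on normality. The multivariable step is the only adjusted analysis: "A multivariate analysis will be performed using a logistic regression analysis to add the covariates that could skew the main association under analysis". The section does not name the dependent variable of that model, a cut-off, or whether the model is binary or ordinal.

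Two statements in the Results section bear on the point. One is an expectation for the app as a whole: "Skin NTDs App version 3 is expected to obtain a result of >3 out of 5 points on the uMARS". The other concerns likely predictors: "those variables related to experience in dermatology or the use of mobile technology may be determining factors". The same section expects no difference by sex, work environment, working institution or country.

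**The concern.** The outcome of the secondary aim is a score that the plan itself treats as quantitative when it compares two groups, yet the adjusted analysis uses a model for categorical outcomes. An analyst following the text has to decide what the categories are. With the usual binary model, that means turning the score into high and low at some value, and the article gives none for individual participants.

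The wording about a main association adds to the difficulty. The study has one group, all using the same app, and the aim covers any of the demographic variables. Candidate factors are listed, but none is singled out as the exposure for which the others are to be adjusted.

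What is at stake is how well the secondary aim is answered. According to the Introduction, the aim matters because the developers do not plan to customise the app for different settings. An inefficient analysis could miss real differences between users and so appear to support that choice. Odds ratios for crossing an unnamed threshold would also not tell the developers how many uMARS points a factor is worth.

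**Working it through.** **The plan's own figure.** The Sample Size Calculation section starts from 100 users and assumes 50% dropout: 100 × (1 − 0.5) = 50. This reproduces. It comes from a recommended range of 10 to 100 users, not from a power calculation. The article gives no mean, SD or target difference for the score, so those used below are assumptions.

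**Outcome against model.** The aim names a score, the score is a mean of 1-to-5 ratings, and the two-group tests treat quantitative data as quantitative. The adjusted model is logistic, with no category defined anywhere in the article.

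**Cost of a cut.** For a normally distributed outcome cut so that a proportion *p* lies on one side, the large-sample efficiency relative to a linear analysis is φ(z)² / [p(1 − p)]. Here z is the cut in SD units from the mean and φ is the standard normal density.

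- Median split (z = 0, p = 0.5): 0.3989² / 0.25 = 0.637. About 64% of the information is kept, equivalent to 0.637 × 50 ≈ 32 participants.
- Cut at 3, assuming mean 3.8 and SD 0.6: z = (3 − 3.8)/0.6 = −1.33. The share scoring 3 or less is 0.091, or 4.6 of 50, and efficiency is 0.325.

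Range for the cut at 3, with 50 participants:

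| Assumed mean | Assumed SD | Scoring 3 or less | Efficiency |
|---|---|---|---|
| 3.5 | 0.5 | 7.9 | 0.44 |
| 3.5 | 0.6 | 10.1 | 0.49 |
| 3.8 | 0.5 | 2.7 | 0.24 |
| 3.8 | 0.6 | 4.6 | 0.33 |
| 4.0 | 0.5 | 1.1 | 0.13 |
| 4.0 | 0.6 | 2.4 | 0.22 |

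Over wider assumptions (mean 3.5 to 4.2, SD 0.4 to 0.8), the count runs from 0.1 to 13.3 and the efficiency from 1.5% to 55%.

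**Power.** For two groups of 25, two-sided alpha 0.05 (sidedness is not stated), and a standardised difference *d*:

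| d | Score kept continuous | Median split |
|---|---|---|
| 0.5 | 42% | 28% |
| 0.8 | 81% | 60% |
| 1.0 | 94% | 79% |

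**Model size.** If every listed demographic except the open language answer were entered, the count would be age 1 + gender 3 + country 1 + health-worker type 3 + case frequency 3 + dermatology 2 + environment 1 + institution 2 + mobile technology 2 = 18 parameters. Even a 25/25 split would then give 25/18 ≈ 1.4 participants in the rarer category per parameter. The two suspected factors alone take 2 + 2 = 4 parameters, or 25/4 ≈ 6.3 at that split. The article does not say which of these models is meant.

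**The case against.** The strongest reply is that logistic regression need not be binary. An ordinal (proportional-odds) model uses the ranking of the scores without a cut. It is also the natural regression counterpart of the Mann-Whitney test that the plan already names as its fallback. This stands in part: a reader might infer that the analysis cannot be run as written, and the text does not support that. It does not say binary, but it does not say ordinal either, so the mismatch remains until one is named.

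A second reply is that outcome coding and covariate lists are commonly left to a statistical analysis plan, which is not shown. This also stands in part. A reader might infer that a threshold would be picked after seeing the data, but the article says nothing about timing and a cut could be fixed elsewhere. The choice of model, however, is stated here, and it does not fit the outcome stated here.

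Third, a reader might take 3 points as the intended cut, or suppose that all 18 parameters would be fitted and conclude that separation or gross overfitting must follow. Neither is in the document. The mark of 3 is an expectation for the app overall, not a participant-level endpoint. The wording about covariates that could skew an association implies some selection. The figures for those two cases show what would happen if they were adopted; they do not describe what is planned.

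Fourth, the article does name an association in general terms, demographics with score, and two suspected factors. That is true, but neither factor is designated as the main one.

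**Conclusion.** The concern holds as a mismatch between a stated model and a stated outcome. The only adjusted analysis is logistic, the outcome is a mean-type score, no binary or ordinal form is defined, and no single main association is designated. This conclusion rests on the text alone.

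The size of the harm depends on how the gap is filled. With a binary model, the best case is a median split, which loses about 36% of the information under normality (power at d = 0.8 falls from 81% to 60%). A cut at 3 would keep about 13% to 49% and leave about 1 to 10 low scorers, for means of 3.5 to 4.0 and SDs of 0.5 to 0.6. With an ordinal model, no cut is needed and this loss does not arise. All these figures assume about 50 participants. The article also gives 48 in the Abstract and 98 under Study Design; that inconsistency is a separate matter and does not change this conclusion.

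The point should be fixed but is not critical. It affects one secondary aim. The main aim, describing app quality, is served by the descriptive analysis and the interviews, and the bivariate tests remain available.

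**What to change.** In the Statistical Analysis section:

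1. Replace logistic regression with multiple linear regression of the app quality mean score, with the subjective quality score second. State that robust standard errors will be used, or that a proportional-odds model will be used if the scores are clearly non-normal. Report linear-model coefficients in uMARS points with 95% CIs.
2. Replace the reference to a main association with the associations of interest. Take dermatology experience and mobile-technology knowledge as the main factors, since the Results section already suspects them. Add a short prespecified covariate list that about 50 participants can support.
3. Estimate the remaining demographics one at a time and label them exploratory, so that the aim's reference to any of the demographic information is still met.
4. If a binary endpoint is wanted after all, state and justify its cut in advance.

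The cost is wording only, with no new data or participants. The small downside is that fewer factors are adjusted for one another.
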